### Intervention and control conditions

The intervention physically locates social workers within schools with the aim to build better working relationships with school staff, students and families. Rather than working with students and families from a LA office base, and liaising with and providing advice to education professionals remotely, the social worker is embedded in the school. S1 Appendix shows a logic model that describes three hypothesized mechanisms of impact:

Enhanced school response to safeguarding issuesIncreased collaboration between social worker and school staff, and parentsImproved relationships between social worker and young people

Pathway A is based around regular, good quality, communication between the social worker and school staff. The advice and support given to school staff is hypothesized to increase staff confidence in safeguarding issues and improve the quality of school referrals. Pathway B is about working directly with families and improving relationships between social workers and parents. Pathway C is about working with children and young people directly. Frequent interactions with the social worker enable the young person to trust the social worker and to feel understood and supported. This is theorised to lead to improved school attendance and participation, better management of a young person’s risks and improved outcomes. In all three pathways, improved child and family outcomes are theorized to lead to a reduction of the number of children in care.

Following the pilot evaluations, an intervention manual has been developed (WWCSC, 2020 –available on request from [contact]). This distils the key messages from the pilots into a practical format designed to assist the 21 LAs in delivering SWIS. Its stated aim is to provide “a framework to refine the SWIS Scale-up programme and encourage more consistent and effective integration of social workers into schools”, although the need for flexibility is acknowledged. The manual offers a number of recommendations for implementers. Among them, the following relate to programme delivery:

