Social workers should be embedded within secondary schools, but can work with feeder primaries.Social workers linked to schools should be experienced (being in practice for at least 2 years).The focus should be on statutory social work with additional opportunities for “preventative” aspects, which could involve “advising staff, families and young people” and working with children who are not at the threshold for formal involvement.Caseloads should be managed by the SWIS team manager and be in line with LA averages, and where possible the carry-over of existing caseloads prior to the launch should be minimal. To avoid disrupting existing relationships SWIS workers are expected to take on new cases.Social workers should be embedded in schools as far as possible, with their own office space in the school and opportunities to integrate.Face to face contact should be the basis for the intervention, in order to build strong relationships with school staff, children and families.

The control group will receive service as usual. Children who are deemed by school staff to require the involvement of CSC will be referred to the LA, usually via telephone call or email to a Multi-Agency Safeguarding Hub arrangement or a referral and assessment team. Children judged by CSC to meet the threshold for involvement will be allocated a social worker as usual, but social workers will not be based in the school. This was chosen as the comparator because it is the status quo that the intervention can be distinguished from, and the system that SWIS needs to perform better than if it is to be considered worthwhile. Children who are deemed to require the involvement of CSC will continue to be eligible for this across all schools, including the control group. LAs will make case by case judgements about the best interests of children who were receiving a service prior to the trial. For example, a child on an existing child protection plan may retain their previously allocated social worker to avoid disruption, rather than transferring to the SWIS worker.

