### Data collection

#### Plans for assessment and collection of outcomes

A proforma will be supplied to the LA, who will complete and return it to the research team at each data collection time point. This process will be trialled in January 2021 prior to quarterly data transfers thereafter. Data relating to the economic evaluation (e.g. salary costs, recruitment costs and some activity time data) will also be collected in this way. Other data items required for the economic evaluation will be collected directly from individual social workers through online surveys (e.g. activity time spent implementing the intervention).

Educational outcome data will be collected from the NPD and made available anonymised at an individual-level (identifiers will be stripped from the dataset) [7]. One application will be made to the NPD in early 2023 to request the required datasets. As per the current timescales for the trial, listed below, it will be possible to access KS4 attainment and attendance data for the trial cohort and report in January 2024.

Date            Milestone

July 2022                        Intervention endsJanuary 2023            Interim report: impact on CSC outcomes, IPE and economic analysisApril 2023            Key Stage 4 and Absence data releasedJuly 2023            Days in Care (35m) data collection endsJanuary 2024            Final report: impact on educational and days in care outcomes

Data for the IPE will be collected primarily through online surveys and interviews. Online surveys of social workers and school staff (five surveys, one at the end of each term, all school social workers and all head teachers in intervention group invited; n = 144 social workers and circa 100–200 school staff) to gather programme-level data on implementation and attitudes and to assess how SWIS is implemented in each school (RQ6 and 8). These will be short, taking no more than fifteen minutes to complete, and administered via Qualtrics online survey platform. Interviews will form part of purposive LA case studies (n = 9; one set of 3 in terms 1–3).

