#### Other secondary analyses

A secondary analysis will use per-term (or per-month, if available) outcome data and include term (or month) as an additional covariate in the model to explore potential implementation effects and/or seasonality. Another secondary analysis will assess the hypothesised mediators of change outlined in logic model (S1 Appendix) at the 23-month follow-up by fitting an interaction term between allocation and category of implementation fidelity (a Gold, Silver, Bronze categorisation will be developed based on a re-analysis of pilot data and other insights from the IPE). Any other subgroup analyses (e.g. by age group) will be agreed with service user input. The p-values generated from these secondary and subgroup analyses will also be adjusted for multiplicity using Hochberg’s step-up procedure. We will fit a two-level mixed-effects model with random LA effects as an additional robustness analysis.

Missing outcome data will not be replaced in the primary analysis, but we will perform null imputation for missing covariates, where we will replace missing values with 0, and create a dummy indicator for the covariate coded 1 if the value was missing, and 0 otherwise, and include the dummy in the regression. If more than 5% of outcome data are missing, we will consider repeating the primary analysis after multiple imputation. To assess the impact of non-compliance (if present), we will exclude intervention arm schools that did not adopt the intervention at all and then repeat the primary analysis, and we will also perform a complier average causal effect (CACE) analysis. Statistical code and anonymised data can be provided upon reasonable request, in line with Centre for Trials Research policy.

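### The planned allocation-by-fidelity interaction does not test the logic-model mediators, and if fidelity is graded per school it reduces to a non-randomised comparison

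*Protocol article*

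**What the plan says.** Other secondary analyses states the purpose first: "Another secondary analysis will assess the hypothesised mediators of change outlined in logic model". It then gives the method, "fitting an interaction term between allocation and category of implementation fidelity", at the 23-month follow-up. The category is described as follows: "a Gold, Silver, Bronze categorisation will be developed based on a re-analysis of pilot data and other insights from the IPE". It has three levels. None is defined for schools without SWIS, and the level of grading (school or LA) is not stated.

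Three other places bear on this:

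- Intervention and control conditions refers to a "logic model that describes three hypothesized mechanisms of impact": the school's response to safeguarding issues, collaboration with staff and parents, and relationships with young people.
- The same section describes the comparator: "The control group will receive service as usual", and in those schools "social workers will not be based in the school".
- Plans for assessment and collection of outcomes describes the implementation surveys, with "all school social workers and all head teachers in intervention group invited". Part of their aim is "to assess how SWIS is implemented in each school".

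Other secondary analyses also plans an analysis that excludes intervention schools which did not adopt SWIS at all, and a CACE analysis.

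**The concern.** The stated purpose, the model term and the moderator do not fit together. The purpose is mediation, the term is an interaction, and the moderator is a grade of how well SWIS was delivered. That grade arises after randomisation and, on the natural reading, has no meaning in a control school.

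The result will be read as evidence on mechanism. RQ7 asks what evidence there is for the mechanisms in the logic model. The Discussion expects the secondary and exploratory analyses fed by the process evaluation to matter more because of Covid-19. If Gold schools show lower rates than controls, the report could present that as support for the logic model. It could equally arise because schools able to implement well already differed from the rest.

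**Working it through.** The protocol gives no figure to reproduce here. The check has two parts.

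**1. Does the analysis address mediation?** A mediation analysis estimates the part of the allocation effect that passes through a measured mediator. It needs a measure of that mediator and a model for it. The logic model's mediators are the three mechanisms listed above. Fidelity category is not among them. An interaction coefficient answers a different question, namely whether the allocation effect differs between levels of another variable. This holds whatever the level of grading.

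**2. Is the interaction identifiable?** Let A = 1 for SWIS and 0 for control, and let B, S and G be indicators for Bronze, Silver and Gold. If fidelity is graded per school, S and G can be non-zero only when A = 1. Hence A×S = S and A×G = G in every row. Rank was computed for 280 schools at 1:1, without covariates:

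| Coding | Columns | Rank | Reason |
|---|---|---|---|
| 1, A, S, G, A×S, A×G; controls set to 0 | 6 | 4 | two duplicate columns: 6 − 2 |
| Controls as a fourth level (B, S, G and their products with A) | 8 | 4 | three duplicates, and A = B + S + G: 8 − 3 − 1 |
| The protocol's null imputation with a missing indicator | 7 | 4 | two duplicates, and the indicator = 1 − A: 7 − 2 − 1 |
| Controls missing and dropped | 6 | 3 | two duplicates, and A is constant: 6 − 2 − 1 |
| Nested: 1, A, A×S, A×G, no fidelity main effect | 4 | 4 | full rank |
| Fidelity defined in both arms | 6 | 6 | full rank |

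At most four quantities can be identified: one control mean and three intervention-arm category means (1 + 3 = 4).

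The nested model shows what would be estimated. On the log-rate scale its coefficients are:

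- A: Bronze minus control;
- A×S: Silver minus Bronze, both within the SWIS arm;
- A×G: Gold minus Bronze, both within the SWIS arm.

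A genuine interaction for Gold against Bronze would be (Gold SWIS − Gold control) − (Bronze SWIS − Bronze control). The two control terms do not exist. The coefficient called an interaction is therefore a difference between groups of SWIS schools formed after randomisation, and each category-against-control contrast compares such a group with all controls.

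**LA-level grading.** If the category were assigned to LAs, it would apply to both arms. With 21 LA effects, allocation and two allocation-by-category terms, the model has 21 + 1 + 2 = 24 columns and rank 24. The category main effect is absorbed by the LA effects, and the interaction is estimable.

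**The case against.** The best defence is that the level of grading is not stated. LAs deliver SWIS, are the randomisation blocks and are the units of the process-evaluation case studies. An LA-level category would make the interaction estimable, with a randomised comparison of arms inside each category. This stands as a possibility. However, no section states an LA-level category, and the surveys are said to assess implementation school by school, so school level is the likelier reading. Even at LA level the result would be effect modification, not mediation.

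A reader might also draw stronger conclusions that the documents do not support:

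- *That the model would fail to run.* The protocol mentions an interaction term but no separate fidelity main effect, and the nested coding is full rank. The difficulty is what the fitted contrast means.
- *That mediation is impossible because the mediators are surveyed only in the intervention arm.* The survey description ties those surveys to RQ6 and RQ8. Mechanisms are RQ7, and this condensed article does not say how every mechanism is measured.
- *That the bias has a known size.* Any rate ratio offered for Gold against control with no true effect would restate an assumed difference in underlying risk. The primary model also adjusts for LA, 2018/19 s.47 enquiries and % eligible for free school meals (FSM), so only confounding left after such adjustment is at issue.

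It is fair to add that this is one secondary analysis. The effectiveness conclusion rests on the intention-to-treat rate ratio for the primary outcome.

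**Conclusion.** The concern holds in two steps of different strength. That the analysis does not assess the mediators is certain from the text, because fidelity is not one of the three mechanisms and an interaction estimates no indirect effect. That the interaction cannot be separated from a fidelity main effect (rank 4 of 6) depends on grading per school, which is the likelier reading but is not stated. On that reading the estimable contrasts are non-randomised and open to residual confounding, in a direction and amount that the documents do not allow one to quantify. The planned non-adopter exclusion and CACE analysis deal with non-compliance; neither repairs this analysis or tests mechanisms. It should be corrected before analysis, but it does not threaten the primary result.

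**What to change.** 1. Remove the statement that this analysis assesses the mediators of change.
2. State whether Gold/Silver/Bronze is assigned to schools or to LAs.
3. If to schools, replace the interaction with an exploratory fidelity analysis: either categories compared within the SWIS arm, or nested contrasts against control. Adjust for LA, 2018/19 rate, % eligible for FSM and school size. Report it as a non-randomised association and not as evidence of mechanism. Comparing within the SWIS arm does not remove the confounding, so the label matters under either option.
4. Keep an allocation-by-category interaction only if the category is defined at LA level and so applies to both arms, and describe it as effect modification.
5. Use the CACE analysis already planned as the causal adherence estimate.

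Taking the exploratory fidelity analysis out of the Hochberg-adjusted set is optional.

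The cost is a change of wording with no new data. The downside is that the mechanism result becomes descriptive.

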### Sample size

At the study design stage, the funder advised that a minimum of 280 mainstream schools would be available to be randomised. Assuming an average of 925 students per school, an average base rate of 12.6 s.47 enquiries per 1000 students per school year under usual practice conditions, and a between-school coefficient of variation of 0.45 within LAs (these estimates are all based on comparator school data from the three pilot studies in Lambeth, Stockport and Southampton) [4], randomising 140 mainstream schools to each group provides 90% power to detect a decrease in rates from 12.6 to 10.48 per 1000 pupils per school year (i.e. a rate ratio of 83.2%). This is using a two-sided 5% type I error level when using a Poisson regression model accounting for cluster randomisation [8].

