### Statistical methods

#### Statistical methods for primary and secondary outcomes

All primary analyses will be ‘intention to treat’ i.e. schools will be analysed in the groups to which they were randomised, regardless of adherence to the intervention. Missing outcome data will not be replaced. For the primary outcome analysis, a quasi-Poisson regression model will be fitted with fixed effects for LAs and cluster robust standard errors reflecting the clustering structure (schools within LAs) to compare rates of s.47 enquiries at 23 months by arm, using the number of students per school as the exposure scaling variable, and s.47 enquiries for 2018/19 (baseline) and % eligible for FSM as fixed-effect covariates. Using a quasi-likelihood model accounts for possible over- or underdispersion i.e. variance in the data that is higher or lower than expected under the standard Poisson model. Allocation will be included in the model as a fixed effect, and the intervention effect (model coefficients transformed into rate ratios) will be presented as point estimate with two-sided 95% confidence interval (CI) and p-value. If the estimated rate is lower in the SWIS arm than in the comparator arm and the 95% CI around the estimated rate ratio excludes the null effect (rate ratio = 1), effectiveness of SWIS at the 5% level will be concluded.

Secondary outcomes will be analysed in a similar way as the primary outcome, by fitting regression models with cluster robust standard errors depending on the type of outcome: quasi-Poisson for rates (referrals to CSC, s.17 assessments) and linear for continuous variables (days in care, educational attendance and attainment). For the school-level variables (referrals to CSC, s.17 assessments, days in care) we will include the same fixed-effect covariates in the model as for the primary outcome (allocation, LA, baseline outcome from 2018/19, % eligible for FSM) and also use the number of students per school as the exposure scaling variable. For the student-level variables (educational attendance and attainment) we will additionally include gender and ethnicity as covariates, and the baseline outcomes used will be 2018/19 attendance (for attendance) and KS4 results (for attainment). The p-values generated from the secondary outcome analyses will be adjusted for multiplicity using Hochberg’s step-up procedure.

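### Dropping never-adopting schools from the SWIS arm only gives a comparison that randomisation does not protect; the planned CACE analysis should carry the non-compliance question

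*Protocol article*

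**What the plan says.** Under Statistical methods for primary and secondary outcomes, the primary analysis is by intention to treat: "schools will be analysed in the groups to which they were randomised, regardless of adherence to the intervention". The decision rule belongs to that analysis. If the estimated rate is lower under SWIS and the 95% CI for the rate ratio excludes 1, "effectiveness of SWIS at the 5% level will be concluded". The model has LA fixed effects, the number of students as exposure, and "s.47 enquiries for 2018/19 (baseline) and % eligible for FSM as fixed-effect covariates".

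Under Other secondary analyses, one sentence sets out two responses to non-compliance, should there be any. The first is "we will exclude intervention arm schools that did not adopt the intervention at all and then repeat the primary analysis". The second follows directly: "we will also perform a complier average causal effect (CACE) analysis". The article defines no matching exclusion for the control arm and attaches no caution to the first analysis.

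**The concern.** Whether a school adopts SWIS becomes known only after randomisation, and only in the SWIS arm. Control schools are never offered a school-based social worker, so those that would not have adopted one cannot be found and removed. After the exclusion, the SWIS arm holds adopters only, while the control arm still holds would-be adopters and would-be never-adopters together.

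If never-adopting schools have a different underlying s.47 rate, for example because of pressure or staffing problems, the trimmed comparison moves away from 1 even when SWIS does nothing. At stake is a supporting result, printed beside the ITT and CACE results, that may disagree with both for reasons unrelated to SWIS and that carries no warning.

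**Working it through.** **Inputs.** From Sample size: 140 schools per arm, 925 students per school, 12.6 enquiries per 1000 students per school year, between-school coefficient of variation 0.45, and a target rate ratio of 10.48/12.6 = 0.832. The article gives neither f (share of schools that never adopt) nor r (their s.47 rate relative to adopters). Assumed ranges: f from 2% to 20%, r from 0.7 to 2.

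**Step 1. The plan's own figure.** The article gives no figure for non-compliance. The nearest is the power statement: "randomising 140 mainstream schools to each group provides 90% power to detect a decrease in rates from 12.6 to 10.48". The standard formula for cluster-randomised rates is Var = [(λ0+λ1)/y + k²(λ0²+λ1²)]/c. With λ0 = 0.0126, λ1 = 0.01048, k = 0.45, c = 140 and y = 925, the standard error is 0.000753, z = 0.00212/0.000753 = 2.82, and power is 80.4%. With 23 months of exposure it is 86.3%. So 90% was not reproduced this way. The article's cited method was not available to check, and nothing below depends on the power figure; only the inputs are carried forward.

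**Step 2. Expected rate ratio with no true effect, unadjusted.** Randomisation puts about the same share f of would-be never-adopters in each arm. If adopters have rate λ, the control mean is λ[(1−f)+fr] = λ[1+f(r−1)], and the trimmed SWIS mean is λ. Hence RR = 1/[1+f(r−1)].

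For f = 10%, r = 1.5: RR = 1/1.05 = 0.952, and ln(0.952)/ln(0.832) is about 27% of the planned log effect. With 126 SWIS schools left, SE(log RR) = √{[1/(925×0.0126) + 0.45²]×(1/140 + 1/126)} = 0.066. The chance of a nominally significant benefit is Φ(−1.96 + 0.049/0.066) = 11.1%, against 2.5%.

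| f | r | RR | false benefit | false harm |
|---|---|---|---|---|
| 2% | 1.5 | 0.990 | 3.5% | 1.7% |
| 5% | 1.25 | 0.988 | 3.8% | 1.6% |
| 5% | 1.5 | 0.976 | 5.7% | 1.0% |
| 10% | 0.7 | 1.031 | 0.8% | 6.7% |
| 10% | 1.0 | 1.000 | 2.5% | 2.5% |
| 10% | 1.5 | 0.952 | 11.1% | 0.3% |
| 20% | 1.5 | 0.909 | 28.8% | below 0.1% |

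Simulation without adjustment (1,000 trials per scenario, 280 schools, gamma-Poisson counts, robust standard errors) agreed: 0.955 and 11.9% at f = 10%, r = 1.5; 0.910 and 30.9% at f = 20%, r = 1.5.

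**Step 3. Allowing for the covariates.** The repeated model keeps the baseline count, % FSM and LA, so Step 2 gives the upper value of the bias for each pair of f and r.

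- Adjusting for a baseline count that shares the school's stable rate: f = 10%, r = 1.5 gives 0.991 and 3.3% false benefit; f = 20%, r = 1.5 gives 0.981 and 7.5%; f = 10%, r = 0.7 gives 1.011 and 6.0% false harm.
- Adding LA terms and varying how far school rates persist from 2018/19, at f = 10%, r = 1.5: one set of simulations gave 0.954 (baseline uninformative) to 0.979 (fully stable), with false benefit of about 10% to 14%. Another (400 trials per scenario) gave 0.953 to 0.990, with about 14% to 6%.

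For f = 10%, r = 1.5 the range is therefore about 0.95 to 0.99, with false benefit of about 3% to 14%. These percentages are rough: in the 1,000-trial runs the ITT analysis itself gave between 1.7% and 4.3% where 2.5% is nominal.

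**Step 4. Keeping the randomised groups.** The simulated ITT rate ratio was 1.00 in every scenario. On the rate-difference scale, CACE is the ITT difference divided by (1−f), so with no effect it is 0/(1−f) = 0, given the exclusion restriction.

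**The case against.** The strongest defence is that this analysis decides nothing. It is conditional on non-compliance occurring, it has no decision rule, and the effectiveness claim rests on ITT. CACE is already planned beside it, and showing ITT, exclusion and CACE results together is common practice. CACE also rests on assumptions. All of this stands. It limits the weight of the point and means that labelling the exclusion is an acceptable alternative to deleting it. It does not make the trimmed comparison valid. The setting also suits CACE: control schools have no school-based social worker, so non-compliance is essentially one-sided, and a school that never adopted at all makes the exclusion restriction plausible.

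A second defence is that f is likely to be small. The section on adherence expects good adherence, ties funding to compliance and reports that all schools confirmed their commitment; f = 10% would mean 14 of 140 funded schools never starting. If every SWIS school in an LA failed to adopt, that LA's control schools would carry no within-LA contrast under LA fixed effects and would add little bias. This also stands, and it points to the smaller values in the table.

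A third is that the covariates absorb the difference. They do so in part. However, according to Amendments to the study, 2018/19 was chosen because it predates Covid-19, so pressure or staffing loss arising in the pandemic is not captured by that baseline.

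Three stronger readings are tempting, and the documents do not support them. A reader might infer that the trial's false-positive rate is inflated; it is not, because the decision rule uses the ITT analysis. A reader might infer that the exclusion favours SWIS; nothing in the article fixes the direction. A reader might also take the Discussion's remark that secondary analyses will gain importance as referring to this analysis. That remark concerns analyses fed by the process evaluation, which fits the planned fidelity interaction more directly, and variable implementation is not the same as complete non-adoption.

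**Conclusion.** The point holds for a supporting analysis only. The one-arm exclusion compares a selected group with an unselected one. It is biased if never-adopting schools differ in s.47 rate beyond what baseline count, % FSM and LA explain, and it is unbiased if they do not. The direction is unknown.

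The size rests on assumed f and r. At f = 10%, r = 1.5 the null rate ratio is 0.952 unadjusted, as the upper value, and about 0.95 to 0.99 after adjustment, according to how stable school rates are from 2018/19. At f = 2% even the unadjusted value is 0.990 for the same r. The ITT conclusion on effectiveness is untouched. The change is worth making because the article states the exclusion without caution and already contains a better analysis of the same question.

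**What to change.** Name the CACE analysis as the analysis of non-compliance, with random allocation as the instrument and the same covariates as the primary model. Then either delete the one-arm exclusion, or keep it as a descriptive result labelled as not protected by randomisation, with no claim of effectiveness drawn from it. If it is kept, report the number of excluded schools and their 2018/19 s.47 rates beside those of the schools retained, so that readers can judge the selection.

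No new data, schools or follow-up are needed. The only cost is the loss or demotion of one familiar supporting analysis.
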